**Possible effects of treatment**

The main clinical manifestation of HSP is a pyramidal pattern of slowly progressive weakness^5^associated with lower limb weakness and progressing to other manifestations, such as dementia, peripheral neuropathy, Parkinson's disease and ataxia.

The aim of VR with virtual reality is to delay the progression of the disease, providing a differentiated, accessible, low-cost treatment option. The use of virtual reality with Nintendo Wii® is a novel, playful, multisensory tool for balance training that engages the patient with enthusiasm and motivation during the continuous sessions. This technological resource is an additional tool to other conventional methods of VR.

**Data analysis**

Data analysis will involve repeated-measures ANOVA with the level of significance set at 5%.

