**Study population**

Forty patients with a diagnosis of HSP will be recruited from the hospital of the Federal University of Parana in the city of Curitiba, Brazil. To participate, the volunteers must meet the following eligibility criteria:

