**Vestibular assessment**

Subsequently, they will carry out the evaluation by the physiological profile (PPA) and Lafayette dynamometer, and application of 10 questionnaires / scales described below before the rehabilitation (1st evaluation) and after the 20th rehabilitation session 2nd assessment), to observe the post- intervention.

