**Randomization**

Prior to the intervention, the volunteers will be randomly allocated to two different groups. Randomization will be performed by an independent researcher using a simple lottery system with sealed opaque envelopes immediately after the baseline assessment. The volunteers will be considered participants in the study the moment the envelope is opened. The participants will be randomized to receive the following distinct interventions:

Group I: Twenty volunteers will undergo VR with virtual reality (balance games) using the Wii® console, Wii-Remote and Wii Balance Board (Nintendo).

Group II: Twenty volunteers will undergo VR with virtual reality (balance games and muscle strength games) using the Wii® console, Wii-Remote and Wii Balance Board (Nintendo).

The games will last from 30 minutes to one hour, with sessions twice a week for 10 weeks (total: 20 sessions).

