**Treatment**

All participants will receive orientation regarding the rehabilitation procedure. The VR will involve virtual reality with the use of the Wii Fit Plus®, Wii-Remote and Wii Balance Board (Nintendo). The Wii Balance Board (WBB) is a platform with sensors that detect the position and orientation of the gamer. In some games, the player must perform the same movement he/she would do in a real game. The VR with virtual reality games will be performed in both groups for 30 minutes twice a week for a total of 20 sessions. Group I will play five balance games. Group II will play the same five balance games plus four strength games. The games will be selected to favor changes in balance and postural instability. After completing the collection of all data, to ensure the same rehabilitation for both groups, will be available the training with strength exercises to group I.

The following are the balance games performed on the WBB:

Soccer Heading®

Table Tilt®

Tightrope Walk®

Penguin Slide®

Perfect 10®

The muscle strengthening exercises were selected to improve balance, which depends on the interaction between vision, vestibular and peripheral sensations, central commands and neuromuscular responses:

Single leg extension®

Torso Twist®

Sideways Leg Lift®

Single Leg Twist®

The training phases will be performed simultaneously, avoiding complications and alterations that may compromise the validity of training. The assessment will be performed again after the 20 intervention sessions.

The time schedule of enrolment, interventions, assessments and visits for participants are describe in Table 2 in accordance of Spirit checklist (Figure 1)

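### With one baseline and one post-treatment value, the planned repeated-measures ANOVA compares the arms by change scores; ANCOVA on the baseline already collected is a free gain in precision, of a size that depends on an unstated correlation

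*Protocol*

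**What the plan says.** The Data analysis section is one sentence: "Data analysis will involve repeated-measures ANOVA with the level of significance set at 5" per cent. It names no model term as the test of treatment and no covariate.

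The rest of the design is clear:

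- **Two assessments.** The Vestibular assessment section places them "before the rehabilitation (1st evaluation) and after the 20th rehabilitation session 2nd assessment". The Treatment section agrees: "The assessment will be performed again after the 20 intervention sessions".
- **Baseline comes before allocation.** The Randomization section has allocation made "using a simple lottery system with sealed opaque envelopes immediately after the baseline assessment". Each baseline score is therefore a true pre-randomisation covariate.
- **Size.** "Forty patients with a diagnosis of HSP will be recruited", and the Randomization section puts twenty in each group. The Timeline section says that recruitment is complete.

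The protocol gives no power, effect size, standard deviation or baseline-to-follow-up correlation, and it mentions no baseline adjustment.

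**The concern.** Repeated-measures ANOVA suggests a method that uses the repeated measurements well. With only two of them, the term that compares the arms over time, group-by-time, is a comparison of mean changes. A change score subtracts the whole baseline value, whatever its correlation with follow-up. ANCOVA subtracts only the part of the baseline that predicts follow-up. The change score therefore carries extra noise whenever the correlation is below 1.

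Two things are at stake. The first is precision: there are 40 patients and recruitment is closed, so the analysis is one of the few places left to gain it. The second is the estimate in the one allocation that actually occurred. If the arms differ at baseline by chance, the change-score estimate moves in the opposite direction, and ANCOVA removes that shift.

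**Working it through.** **Inputs from the protocol.** 20 patients per arm (Randomization); two assessments (Vestibular assessment, Treatment); 5% level (Data analysis). The protocol does not say whether the test is one- or two-sided; two-sided is assumed here, as an F test implies.

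**Assumed inputs, not in the protocol.** A true difference of d = 0.7 outcome SDs; correlation r from 0.3 to 0.9; equal SD at both times. There is no stated power figure to reproduce.

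**Step 1: what group-by-time tests.** In a simulated data set of 20 + 20 patients with two values each, the group-by-time F on 1 and 38 degrees of freedom was 17.108. The squared t statistic on change scores was also 17.108. They are the same test.

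**Step 2: variances.** Take the outcome variance as 1.

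- Change score: 2(1-r)
- ANCOVA: 1-r² = (1-r)(1+r)
- Ratio of ANCOVA to change score: (1-r)(1+r) / [2(1-r)] = (1+r)/2, which is below 1 for every r below 1

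The number of patients that a change-score analysis needs to match ANCOVA with 40 is 40 × 2/(1+r).

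**Step 3: power.** Noncentral t, with noncentrality d / [SD factor × √(2/20)], where √(2/20) = 0.316. The change score has SD factor √(2(1-r)) and 38 df. ANCOVA has √(1-r²) and 37 df. At r = 0.5 the noncentrality is 0.7/(1.000 × 0.316) = 2.21 for the change score and 0.7/(0.866 × 0.316) = 2.56 for ANCOVA.

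| r | Variance ratio (1+r)/2 | Power, change score | Power, ANCOVA | Change-score patients equal to 40 under ANCOVA |
|---|---|---|---|---|
| 0.3 | 0.65 | 45% | 62% | 62 |
| 0.5 | 0.75 | 58% | 70% | 53 |
| 0.7 | 0.85 | 80% | 86% | 47 |
| 0.8 | 0.90 | 93% | 95% | 44 |
| 0.9 | 0.95 | over 99% | over 99% | 42 |

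**Step 4: cost of estimating the slope.** Beyond the lost degree of freedom, estimating the baseline slope inflates the ANCOVA variance on average by about 1 + 1/36 = 1.028. This takes about one point off the ANCOVA power at r = 0.3 to 0.7 and less above that. The ratio becomes 1.028 × (1+r)/2, which stays below 1 until r is about 72/37 - 1 = 0.95. A separate simulation of 4,000 trials at d = 0.8 gave change score against ANCOVA 70% and 81% at r = 0.5, and 88% and 92% at r = 0.7. The order and rough size of the gain are therefore not artefacts of the formula.

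**Step 5: chance baseline difference.** If the arms differ at baseline by D, the expected difference in follow-up is d + rD. The expected difference in change is d + rD - D = d - (1-r)D. For D = 0.5 SD the shift is 0.25 SD at r = 0.5, 0.15 SD at r = 0.7 and 0.05 SD at r = 0.9. The standard error of a baseline difference is 0.316 SD, so a difference beyond 0.5 SD in either direction (0.5/0.316 = 1.58 standard errors) has a chance of about 11% on any one instrument.

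**The case against.** The strongest reply is that nothing here is an error. In a randomised trial the change-score test holds its 5% level and is unbiased over randomisations. The sentence contradicts nothing, and covariates are often left to an analysis plan, which may exist and is not shown. The validity point stands in full, and it limits the concern to efficiency and to the conditional shift in Step 5. The last part stands only partly. The protocol does name a method, and the point is that a better one is available for this design, not that a detail is absent.

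The size of the gain is also open to challenge. The disease is described as slowly progressive and the programme lasts 10 weeks, so high correlations are plausible for some instruments. At r = 0.8 the gain is about 2 points and at 0.9 it is nil. This stands.

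Three stronger readings are tempting, and the document does not support them.

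- **That the trial would be tested on the group main effect.** That term averages in the pre-treatment value and halves the expected effect, so its power at 0.7 SD would be only about 22% to 24% at r = 0.5 to 0.7. The protocol never says it will test that term. The Assessment of results section frames the outcomes as pre-to-post improvement, which points to change over time.
- **That a baseline imbalance is likely.** At about 11% per instrument for a difference beyond 0.5 SD, it is possible but not expected on a given outcome.
- **That change scores give a biased result.** The shift is conditional on the imbalance observed and averages to zero over allocations.

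It can also be said that ANCOVA does not settle multiplicity across the ten primary tools, or the scale of scores such as the VADL, which is a median of item scores. That is true, but repeated-measures ANOVA faces the same questions.

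**Conclusion.** The point holds as a free improvement, not as a flaw in validity. The algebra is certain: with two time points the planned between-arm test is the change-score test, and ANCOVA has (1+r)/2 of its variance. The benefit in this trial is not certain, because r and the effect size are assumptions. At 0.7 SD and 20 per arm the gain in power is about 17 points at r = 0.3, 12 at 0.5, 6 at 0.7, 2 at 0.8 and none at 0.9. Among the correlations examined, ANCOVA is never worse in any way that matters, and it removes the shift from a chance baseline difference. A reader should not infer that a result from the planned method would be invalid.

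**What to change.** Replace the sentence in the Data analysis section with wording such as: *Each outcome at the second assessment will be compared between the randomised groups by ANCOVA, with group as factor and the baseline value of the same outcome as covariate. The adjusted mean difference will be reported with its 95% confidence interval and tested at the two-sided 5% level. Repeated-measures ANOVA will be given as a descriptive supplement.*

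This also names one between-arm contrast, which the present sentence does not. Make the change before any comparison by arm has been seen. The cost is a short rewording and one residual degree of freedom (37 instead of 38), with no new data, visits or patients.

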**Control of bias**

The study includes several important methodological resources that will minimize the risk of bias, such as the randomization process, allocation concealment, blinded assessment of the results and intention-to-treat analysis.

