**Quality of life**

The Quality of Life Group of the World Health Organization (WHO) developed the short version of the WHOQOL-100 denominated the WHOQOL-Bref ^16^. This version is a useful alternative to the long version, as the proposed study will involve several assessment tools. The questionnaire is used to determine the perceptions of individuals about your health and can be used to assess the quality of life of different populations and in different situations^17.^

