**ABC Activities-Specific Balance Confidence (ABC) scale**

The ABC scale, translated and adapted to the Brazilian population^19^, showing good quality, discriminating validity, consistency and reliability^20^.It has 16 items for assessing balance during a set of activities of daily living (ADLs) of medium difficulty^21^. The confidence for each ADL is measured by the volunteer, choosing a percentage point on a scale ranging from 0% (without confidence) to 100% (total confidence). A total greater than 80% corresponds to a high functional level, 50 to 80% moderate physical functioning and a score below 50% indicates a low functional level^22^.

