**Falls Efficacy Scale – International (FES-I)**

The FES-I is a self-administered questionnaire designed to evaluate the fear of falling during a set of activities. It is composed of 16 items scored from 1 to 4 points, with higher scores denoting a great fear of falling during a given activity. The FES-I has internal consistency of 0.96. Moreover, most items enable differentiating individuals who have suffered a fall, those who have suffered two or more falls and those who have not fallen^34^.The version validated for the Portuguese language will be used^35^.

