**Assessment of results**

The participants will be evaluated by an independent examiner who will be blinded to the allocation to the different groups. The primary outcomes will be evaluated with each of the assessment tools, considering an improvement in the performance in the comparison of the pre-intervention and post-intervention assessment:

PPA: quantifies the risk of falls.

Dynamometer: verification of improvement in muscle strength;

WHOQOL-Bref: improvement in perceived quality of life in different domains;

BBS: analysis of balance status;

ABC: like BBS, verifies balance, but related to activities of daily living;

VADL: investigates impact of dizziness and balance on degree of dependence;

MMSE: measures degree of cognitive impairment;

TUG test: measures risk of falls related to muscle weakness;

FES-I: investigates fear of falling;

VAS: quantifies pain intensity.

The secondary outcomes will quantify the improvement in performance on the assessment. For such, a specific questionnaire will be administered for each assessment.

Secondary outcome 1: Improved locomotion capacity, increased stability during gait, reduction in gait deviations; evaluated using TUG test and BBS.

Secondary outcome 2: Increased spatial orientation capacity; evaluated by PPA, WHOQOL-Bref, ABC scale and MMSE.

Secondary outcome 3: Reduction in falls;evaluated by FES-I, ABC scale, VADL scale and dynamometer.

Secondary outcome 4: Improved capacity to perform activities of daily living, generating self-confidence that will lead to positive gains in aspects of family, social and professional life; evaluated by WHOQOL-Bref, VAS and VADL scale.

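### Blinded assessment is claimed for the results as a whole, but is unsupported for the 3 to 5 of 10 primary outcomes that unblinded participants rate themselves

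*Protocol*

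**What the plan says.** The Control of bias section names "allocation concealment, blinded assessment of the results and intention-to-treat analysis" as features that reduce the risk of bias. It does not restrict the blinding to particular outcomes.

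The Assessment of results section says who is blinded: participants will be "evaluated by an independent examiner who will be blinded to the allocation to the different groups". It continues: "The primary outcomes will be evaluated with each of the assessment tools", and lists ten tools: PPA, dynamometer, WHOQOL-Bref, BBS, ABC, VADL, MMSE, TUG, FES-I and VAS.

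The instrument sections say where some of the ratings come from. On FES-I: "The FES-I is a self-administered questionnaire designed to evaluate the fear of falling". On ABC: "The confidence for each ADL is measured by the volunteer". WHOQOL-Bref is used to "determine the perceptions of individuals about your health". The VAS section describes a line for pain intensity, and the VADL section a scale for the effect of dizziness and imbalance on daily activities. Neither names the rater.

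Under Treatment, Group I plays five balance games and Group II plays the same five plus four strength games. No section says that participants are blinded. The Quality assurance section says that the treating researchers will not know the initial evaluation results; it does not say that they are unaware of allocation.

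**The concern.** Where a scale is filled in from the participant's own perception, the participant is in effect the assessor. A blinded examiner who hands over the form does not blind the answer. The arms differ in a way that participants see at every session, so the self-raters know what they received.

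A group difference on these scales could therefore reflect expectation or reporting, wholly or in part. With the safeguard stated without limit, such a difference could be reported as a blinded primary result. The reach is wider than the primary list. Secondary outcome 4 rests entirely on participant-reported tools (WHOQOL-Bref, VAS, VADL). Three of the four tools for secondary outcome 3 (FES-I, ABC, VADL) and two of the four for secondary outcome 2 (WHOQOL-Bref, ABC) are of the same kind.

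**Working it through.** **Step 1: classify the ten primary outcomes by who supplies the rating.** The source is the protocol's section on each tool.

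| Tool | Source of the rating | Basis |
|---|---|---|
| FES-I | participant | explicit (self-administered) |
| ABC | participant | explicit (rated by the volunteer) |
| WHOQOL-Bref | participant | description (own perceptions) |
| VAS | participant | content (pain intensity); rater not named |
| VADL | participant | content (effect on daily activities); rater not named |
| PPA | examiner | direct sensorimotor testing |
| Dynamometer | examiner | device-measured strength |
| TUG | examiner | stopwatch time |
| BBS | examiner | nature of the test |
| MMSE | examiner | nature of the test |

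Counting only tools whose description points to the participant gives 3 of 10. Adding VAS and VADL by content gives 3 + 2 = 5 of 10.

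**Step 2: set the claim beside the design.** The only blinded party is the examiner. That supports blinded assessment for the five examiner-measured tools. For the other five, the person who produces the rating knows the treatment received.

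**Step 3: illustrate what a reporting shift could do.** The protocol gives no figure for this, so the shift and the correlation are assumptions.

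Inputs: 20 per group (Randomization section); 5% level and repeated-measures ANOVA (Data analysis section), taken here as two-sided; two time points (Vestibular assessment section). Assumed: no true effect; a shift b, in SD units, in the post-intervention self-report of one group relative to the other; equal SDs at both times; pre-post correlation r.

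With two time points, the group-by-time test is equivalent to a two-sample t-test on change scores:

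- SD of change = sqrt(2(1 − r)), in units of the outcome SD
- standardised shift d = b / sqrt(2(1 − r))
- noncentrality = d × sqrt(20/2), with 38 degrees of freedom and critical value 2.024

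The SD of change is sqrt(1.0) = 1 at r = 0.5 and sqrt(0.6) = 0.775 at r = 0.7. For b = 0.3 and r = 0.7, d = 0.3/0.775 = 0.387 and the noncentrality is 0.387 × 3.162 = 1.225, which gives a rejection probability of 22.3%.

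| Assumed shift b | r = 0.5 | r = 0.7 |
|---|---|---|
| 0.1 SD | 6.1% | 6.8% |
| 0.2 SD | 9.5% | 12.5% |
| 0.3 SD | 15.2% | 22.3% |
| 0.4 SD | 23.4% | 35.7% |

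With no shift the rate is 5%. These are rates for a single self-reported outcome.

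**The case against.** **The claim is not false.** A reader might infer that the protocol's blinding statement is untrue. The documents do not support that. The Assessment of results section describes an allocation-blinded examiner, nothing contradicts this, and nowhere are participants said to be blinded. The Control of bias phrase can be read as a short summary of examiner blinding. This stands. What remains is that the phrase covers the results without limit, and so claims more than examiner blinding can deliver for self-rated scales.

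**Participants cannot be blinded to the games they play.** True, and it is a general limitation of exercise trials. It is no reason to describe the self-reports as blinded.

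**Expectation may be weak.** Both arms are active, use the same console, share five games and have the same number of sessions. Knowing one's own games is not knowing the other arm's content or which arm is expected to do better. This may reduce the bias, possibly to very little, but it does not make the rater blinded.

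**The later offer to Group I.** It is tempting to argue that the plan "to ensure the same rehabilitation for both groups, will be available the training with strength exercises to group I" tells Group I that it received the lesser programme. The Treatment section places this offer after all data are collected and does not say when participants learn of it. If they learn of it only then, it cannot affect recorded answers. The consent pages are not in the copy reviewed, so the point is speculative and nothing here rests on it.

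**The size is assumed.** Correct. No source in the protocol fixes the shift or the correlation, and at 0.1 SD the inflation is slight.

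**The count is soft.** VAS and VADL are classified by content, which is why the count is given as 3 to 5.

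**Conclusion.** The concern holds as a limit on the claim. Blinded assessment is supported for the five examiner-measured primary outcomes. It is unsupported for WHOQOL-Bref, ABC and FES-I, and by content for VAS and VADL: 3 to 5 of 10. This conclusion rests only on the protocol's own descriptions and on the visible difference between the arms.

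The range of about 6% to 36% is an illustration of what is possible under the assumed shift and correlation. It is not an estimate of bias in this trial, and the conclusion does not depend on it.

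A reader might also infer that the five self-reported scales should lose their primary status. That does not follow: an imprecise blinding statement calls for a precise one, and the order of the outcomes is a separate decision.

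**What to change.** In the Assessment of results and Control of bias sections:

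1. Limit the blinding claim to the examiner-measured outcomes: PPA, dynamometer, BBS, TUG and MMSE.
2. State that WHOQOL-Bref, ABC, FES-I, VAS and VADL are reported by participants who know which games they played, that group differences on them carry a risk of reporting bias, and that they will not be presented as blinded results.
3. Ask participants not to tell the examiner which games they played. This protects the examiner-measured outcomes; it does nothing for the self-reports.

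The list of primary outcomes can stay as it is. The Timeline section says that recruitment is complete, so the instruction in item 3 can help only at assessments still to be done, while items 1 and 2 can be made at any time before reporting. The cost is wording and a brief instruction, with no extra visits, staff or patients. The downside is that a stated strength of the design becomes less favourable.
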